## Abstract

**Background:**

Despite the availability of evidence-based psychotherapies for depression and anxiety, they are underused in non-mental health specialty settings such as primary care. Hybrid effectiveness-implementation designs have the potential to evaluate clinical and implementation outcomes of evidence-based psychotherapies to improve their translation into routine clinical care practices.

**Methods:**

This protocol article discusses the study methodology and implementation strategies employed in an ongoing, hybrid, type 2 randomized controlled trial with two primary aims: (1) to determine whether a brief, manualized cognitive behavioral therapy administered by Veterans Affairs Primary Care Mental Health Integration program clinicians is effective in treating depression and anxiety in a sample of medically ill (chronic cardiopulmonary diseases) primary care patients and (2) to examine the acceptability, feasibility, and preliminary outcomes of a focused implementation strategy on improving adoption and fidelity of brief cognitive behavioral therapy at two Primary Care-Mental Health Integration clinics. The study uses a hybrid type 2 effectiveness/implementation design to simultaneously test clinical effectiveness and to collect pilot data on a multifaceted implementation strategy that includes an online training program, audit and feedback of session content, and internal and external facilitation. Additionally, the study engages the participation of an advisory council consisting of stakeholders from Primary Care-Mental Health Integration, as well as regional and national mental health leaders within the Veterans Administration. It targets recruitment of 320 participants randomized to brief cognitive behavioral therapy (n = 200) or usual care (n = 120). Both effectiveness and implementation outcomes are being assessed using mixed methods, including quantitative evaluation (*e.g.*, intent-to-treat analyses across multiple time points) and qualitative methods (*e.g.*, focus interviews and surveys from patients and providers). Patient-effectiveness outcomes include measures of depression, anxiety, and physical health functioning using blinded independent evaluators. Implementation outcomes include patient engagement and adherence and clinician brief cognitive behavioral therapy adoption and fidelity.

**Conclusions:**

Hybrid designs are needed to advance clinical effectiveness and implementation knowledge to improve healthcare practices. The current article describes the rationale and challenges associated with the use of a hybrid design for the study of brief cognitive behavioral therapy in primary care. Although trade-offs exist between scientific control and external validity, hybrid designs are part of an emerging approach that has the potential to rapidly advance both science and practice.

**Trial registration:**

NCT01149772 at
http://www.clinicaltrials.gov/ct2/show/NCT01149772

## Background

Traditional cognitive behavioral therapy (CBT), consisting of 12 to 16 sessions over three to six months of treatment, is an efficacious treatment for depression and anxiety
[1-5]. Much of the research on CBT has been conducted in academic trials and within specialty mental healthcare settings
[6,7]. Less is known about the utilization of brief CBT (bCBT), consisting of four to six sessions over a maximum of four months, and its ability to be adopted within non-mental healthcare settings such as primary care. Treatment modalities like bCBT can dramatically enhance the reach of mental illness therapy, given the prevalence and morbidity of depression and anxiety among medically ill patients.

Although psychotherapies such as CBT improve patient outcomes, such treatments are infrequently used within integrated healthcare settings, especially in non-specialty mental healthcare settings such as primary care
[8-11]. In an effort to improve the availability of psychotherapy, the Department of Veterans Affairs (VA) issued the Uniform Mental Health Services Handbook in 2008
[12], which mandated that VA medical centers embed mental health services into primary care settings and make available evidence-based psychotherapies for all veterans with depression and anxiety. Since 2008, the VA has promoted a national dissemination program called Primary Care-Mental Health Integration (PC-MHI) for all its hospitals and large community-based clinics and has also dedicated significant resources toward clinician training in traditional evidence-based psychotherapies, including CBT, using a 12- to 16-session approach
[4,13,14].

Unfortunately, mental health providers in the primary care setting face challenges to implementation of traditional evidence-based psychotherapies. Evidence suggests that patients treated in primary care are distinct from specialty mental healthcare patients (*e.g.*, present with physical health concerns and fewer chronic and severe mental health difficulties) and require modifications to traditional approaches
[15,16]. Data also suggest that primary care patients may benefit from mental health interventions that are less intensive and focus treatment around physical as well as emotional health concerns
[17-19]. These patients may also prefer and engage more fully in care co-located in primary care
[20,21]. Lastly, VA PC-MHI providers require assistance to determine how best to modify traditional evidence-based therapies to better align with the practice demands of the primary care setting, which are increasingly involving collaborations between mental and physical health providers (*e.g.*, medical home or the Patient-Aligned Care Team initiative within the VA). For example, in the VA PC-MHI program, clinicians are asked to provide evidence-based care (*e.g.*, 12–16 sessions of CBT) within an integrated primary care model that encourages psychotherapy services in the range of four to six sessions of care
[11,22,23]. Presently, mental health providers in primary care are struggling to adapt traditional evidence-based approaches, and they need data to support their delivery of high-quality care.

Initial studies provide evidence that bCBT is an effective treatment within primary care for depression, panic, and generalized anxiety disorders
[17,18,24-27]. Although studies support the general efficacy of bCBT, additional effectiveness data are needed to determine the impact of these treatments under real-world conditions and to understand the potential for bCBT to be integrated within primary care.

### Using blended effectiveness-implementation designs to improve the provision of evidence-based psychotherapy

It is imperative that research focus on increasing use of evidence-based interventions in frontline practice
[28]. Unfortunately, significant time and resources are required by the traditional sequential scientific approach that moves from clinical efficacy to effectiveness and then implementation
[29], and this approach is often plagued by practice or translational barriers because of the mismatch between the scientific intervention and the demands of frontline practice
[9]. Hybrid designs are increasingly being used to move science beyond an excessive attention to internal validity. Clinical-intervention hybrid designs are commonly employed on the efficacy/effectiveness continuum
[9,30] and generally provide more relaxed internal controls to improve generalizability. Hybrid effectiveness/implementation (E-I) designs
[31]are relatively new, with distinct methodological opportunities and challenges. Hybrid E-I designs address clinical effectiveness but target the methods and procedures necessary to deliver and sustain interventions in real-world care settings. As a prerequisite, hybrid E-I designs require a minimum of “indirect evidence” supporting a clinical intervention
[31]. Without preexisting evidence to support the clinical intervention, implementation evaluation is premature.

As proposed by Curran *et al.*[31], hybrid E-I studies include a continuum of designs that move from effectiveness research with minimal implementation strategies (type 1) to designs where effectiveness and implementation are equally balanced (type 2) to a largely implementation approach with minimal focus on effectiveness outcomes (type 3) (Figure
1). The determination of which hybrid E-I design to choose is based on current literature and practice patterns.

**Figure 1 F1:**
[figure not shown]
Hybrid effectiveness–implementation designs as part of the clinical research continuum.

Prototypical clinical and implementation research designs do not share many design features. Thus, a series of compromises are needed when creating and conducting a hybrid E-I study to balance the demands associated with scientific control or internal validity and factors associated with implementation, such as evaluation and improvement of processes and systems of care. Although compromise between these competing constructs may prove challenging, hybrid designs have the potential to (1) shorten the existing lag time between research discovery and uptake in care settings, (2) provide additional knowledge of clinical processes and system factors critical to adoption and long-term utilization, and (3) reduce cost by streamlining and combining elements of the traditional step-wise progression of research (efficacy to effectiveness to implementation)
[31]. Most importantly, hybrid E-I designs that use strong and broad-reaching partnerships improve the collective shared vision among stakeholders and, ultimately, improve the odds that interventions developed will be adopted into practice.

Evaluation of hybrid E-I designs involves careful attention to the assessment of outcomes related to both clinical effectiveness and implementation success. RE-AIM is a commonly used framework to aid in addressing the unique challenges of blended E-I designs
[32-36]. RE-AIM seeks to enhance evaluation and reduce the disparities between research, applied clinical practice, and sustainability of evidence-based practices over time
[28,34] by focusing on five components: **R**each (the participation rate of the targeted population), **E**fficacy/**E**ffectiveness (the impact of the intervention on outcome criteria), **A**doption (number or proportion of sites/clinicians who provide the clinical intervention), **I**mplementation (intervention integrity, quality, and consistency of delivery), and **M**aintenance (sustainability of the intervention over time).

This protocol article describes a hybrid type 2 study, entitled “Cognitive Behavioral Therapy in Primary Care: Treating the Medically Ill.” Consistent with the hybrid E-I design
[31] and informed by the RE-AIM framework
[34], the project focuses on the effectiveness of bCBT for patient outcomes related to depression, anxiety, and physical health, while also seeking to simultaneously pilot test the acceptability, feasibility, and preliminary outcomes of a multifaceted implementation strategy to enhance patient engagement, as well as clinician adoption and fidelity. The article highlights study procedures and critical methodological decisions related to conducting a hybrid E-I study for bCBT.

## Methods

The Adjusting to Chronic Conditions Using Education, Support, and Skills (ACCESS) study was developed to examine the clinical effectiveness and implementation potential of an evidence-based, patient-centered bCBT intervention for depressed and/or anxious medically ill veterans. The project is being conducted within the PC-MHI programs of two large VA medical centers in the south central United States. The current study was approved by the Baylor College of Medicine Institutional Review Board (H-27082) and local VA Research and Development review committee. As such the study is in compliance with the Helsinki Declaration and all study participants provided informed consent including permissions for publication of this report.

ACCESS uses a patient-level, randomized design and focuses on veterans with chronic obstructive pulmonary disease (COPD) and/or heart failure (HF). COPD and HF are highly prevalent and burdensome to patients and the healthcare system
[37-39]. These conditions are exacerbated by clinically elevated symptoms of depression and anxiety, which are common in approximately 50% of this patient population
[40-43].

ACCESS seeks to recruit 320 primary care patients with COPD and/or HF and comorbid clinically elevated symptoms of depression and/or anxiety, identified through VA databases and solicited using opt-out letters (see Consort Diagram in Figure
2). Of these, 120 patients will be randomized to usual care (UC) and provided with feedback about their depression and/or anxiety and encouraged to obtain services through their primary care provider. The remaining 200 patients will be randomized by blinded study staff to a bCBT intervention (*e.g.*, ACCESS intervention) provided by frontline mental health clinicians in two VA PC-MHI clinics. PC-MHI clinicians, who are mental health practitioners from various disciplines, including psychology, social work, nursing, and physician assistant backgrounds, will receive a comprehensive set of implementation interventions to enhance use and quality of the ACCESS intervention within their ongoing clinical care clinics. The collective implementation strategy to be pilot tested was created from the research team’s past experience in training clinicians in bCBT procedures and from the available implementation literature. The implementation strategy includes the following interventional components: (1) online clinician training; (2) audit and feedback of clinician session content, as provided by expert review; and (3) internal and external facilitation to support CBT use, including identification of system/clinic barriers.

**Figure 2 F2:**
[figure not shown]
**Study CONSORT diagram illustrating flow of participants from recruitment to random assignment to follow-up.** ACCESS = Adjusting to Chronic Conditions Using Education, Support, and Skills; COPD = chronic obstructive pulmonary disease; HF = heart failure; MH = Mental Health; SDP = Substance Dependence Program; CMHP = Comprehensive Mental Health Program; HBPC = Home Based Primary Care; TRP = Trauma Recovery Program; PCP = primary care physician; NYHA = New York Heart Association; MRC = Medical Research Council Breathlessness Scale; BAI = Beck Anxiety Inventory; PHQ-9 = Patient Health Questionnaire-9.

The study has two primary purposes: (1) to determine the clinical effectiveness of the ACCESS intervention (bCBT) relative to UC on patient outcomes related to symptoms of depression and anxiety and disease-specific physical functioning and (2) to pilot test and examine the acceptability, feasibility, and preliminary outcomes of an implementation strategy designed to improve patient engagement and adherence, as well as intervention quality. Both effectiveness and implementation outcomes (see Table
1 for study objectives) will be assessed, using mixed methods involving qualitative procedures (*e.g.*, focus interviews and surveys conducted with patients and providers) and quantitative analyses (*e.g.*, intent-to-treat analyses and formal session fidelity ratings).

**Table 1 T1:** Study outcomes and objectives

**Outcome**	**Objective**
**Effectiveness**	#1: To determine whether a bCBT treatment group as provided by VA PC-MHI clinicians is superior to a usual-care control group at post treatment and 8- and 12-month follow-ups, as measured by:
	a) depression and anxiety scores (Patient Health Questionnaire-9 and Beck Anxiety Inventory)
	b) cardiopulmonary disease outcomes (Chronic Respiratory Questionnaire and Kansas City Cardiomyopathy Questionnaire).
**Implementation**	#2: To assess bCBT adoption and fidelity, as measured by:
	a) bCBT patient engagement (one or more sessions) and adherence (four or more sessions)
	b) PC-MHI clinician bCBT adherence and competency ratings as evaluated by expert audio session reviews.

*bCBT* brief cognitive behavioral therapy, *VA* Department of Veterans Affairs, *PC-MHI* Primary Care-Mental Health Integration.

### Objective #1: clinical effectiveness of brief cognitive behavioral therapy

Comparative effectiveness trials suggest a general equivalence between CBT and other therapeutic modalities
[44], with CBT being particularly well-suited for implementation within primary care settings, given its skill-based approach and ability to function with a restricted time and session framework
[45,46]. Recent evidence suggests the general efficacy of bCBT for patients in primary care and patients with comorbid health conditions
[17,18,47,48]. However, limited data exist on the real-world effectiveness of bCBT within the primary care setting, especially when used for the chronically medically ill
[49].

### Clinical intervention

The ACCESS intervention is a manualized bCBT protocol that provides a flexible, patient-centered approach to increase patient engagement and adherence, while addressing both the mental and physical health needs of veterans with COPD and HF. ACCESS consists of six weekly treatment sessions and two brief (10- to 15-minute) telephone “booster” sessions within a four-month time frame. Participants are asked to attend the first session in person and can participate in subsequent sessions by telephone or in person.

The ACCESS intervention was developed based on prior studies and input from a variety of stakeholders, including patients, providers, PC-MHI directors, and national CBT experts
[50]. Particular emphasis has been placed on maximizing intervention potency and minimizing session intensity and duration to maximize patient engagement and adoption within PC-MHI settings. Patients initially receive core modules focused on increasing awareness and controlling physical and emotional symptoms and subsequently are able to select skills from a series of module choices best aligned with their most pressing needs. Therapists follow a structured intervention manual, yet retain the ability to streamline and tailor the bCBT intervention collaboratively with patients when selecting treatment modules and goals. A patient workbook is provided to structure session content, guide telephone interactions, and provide opportunities to guide patient practice of skills between sessions.

Following an iterative developmental process
[19,50], the ACCESS intervention was modified to be consistent with the PC-MHI model of the VA of brief four to six sessions of psychotherapy. ACCESS provides clinicians with structure and details that seek to ensure high fidelity to the intervention, while retaining flexibility in administration so as to mirror traditional psychotherapy practices. Data from a previously conducted open trial suggest that ACCESS improves both physical and emotional health outcomes and results in high engagement and adherence
[19]. Detailed descriptive information about the content and processes of the ACCESS intervention can be found elsewhere
[50].

### Identification and recruitment of participants

Study participants are being recruited from the Houston and Oklahoma City VA medical centers, using VA administrative databases to identify COPD and HF patients who received care in the prior year. Houston and Oklahoma City VAs were chosen for their size and integration of primary care mental health within the Veterans Integrated Service Network 16. Opt-out letters are mailed to participants to ensure the widest catchment possible. Interested participants complete a telephone screening process. Participants are included in the study if they are confirmed to have patient-reported functional limitations associated with their COPD and/or HF and have clinically significant symptoms of anxiety and/or depression. Participants are excluded only for clinical factors (*e.g.*, ongoing psychotherapy, concurrent specialty mental healthcare) or patient factors (*e.g.*, cognitive, bipolar, psychotic, or substance use disorders) that would render a PC-MHI bCBT intervention or PC-MHI treatment setting inappropriate
[51]. Patients receiving psychotropic medications are not excluded, although they have their medication use monitored during the course of the study.

Sample size was established to ensure adequate power to detect differences in the primary patient outcomes for depression, anxiety, and physical health. To ensure 80% power to detect differences at the 0.05 level for all study measures, adjusting for repeated measures, a sample size of 180 randomized patients was necessary. However, this sample-size calculation was inflated because of the potential for intraclass correlations related to the clustering of patients within bCBT providers. Using an established inflation factor
[52] and controlling for attrition of 25%, the final sample-size calculation required 200 participants for the ACCESS arm and 120 for UC (320 total). Unequal randomization, an accepted practice in clinical trials
[53], was used to reduce unnecessary recruitment without significant impact on power. Randomization was stratified by medical condition (COPD only, HF only, both COPD and HF) and by site, using random block sizes of 5 or 10. Because of the higher number of patients in Houston, 200 of the 320 total patients will be randomized at Houston and 120 at Oklahoma City. Random allocation lists were generated using SAS statistical software (SAS Institute, Inc., Cary, NC, USA). Randomization numbers are drawn from envelopes stuffed by non-project staff and opened only after a participant is deemed fully eligible and ready for group assignment.

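### The stated arm sizes of 200 and 120 (5:3) do not fit the stated block sizes of 5 or 10, which point to 3:2 and about 192:128

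*Protocol article*

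**What the plan says.** The arm sizes appear in three places in the protocol article: the Methods paragraph of the abstract, the opening part of the Methods section, and the sample-size text under Identification and recruitment of participants. The sample-size text says that "the final sample-size calculation required 200 participants for the ACCESS arm and 120 for UC (320 total"). The opening Methods text assigns 120 patients to usual care and then says: "The remaining 200 patients will be randomized by blinded study staff to a bCBT intervention".

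The randomization is described at the end of Identification and recruitment of participants. The strata are given as: "Randomization was stratified by medical condition (COPD only, HF only, both COPD and HF) and by site". The block sizes follow in the same sentence: "and by site, using random block sizes of 5 or 10". The lists came from SAS, and the allocation numbers are drawn from envelopes prepared by staff outside the project. The same paragraph gives site totals: "200 of the 320 total patients will be randomized at Houston and 120 at Oklahoma City". Those are the same two numbers as the arm sizes, but they describe sites, not arms.

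The article says that allocation is unequal. It does not give the split within a block.

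**The concern.** Permuted blocks fix the allocation ratio: each complete block contributes a whole number of patients to each arm, and the trial's overall ratio follows from those counts. The stated arm sizes and the stated block sizes should therefore describe the same ratio, and here they do not. The arm sizes carry weight, because the sample-size text presents them as the result of the calculation. A reader cannot tell from the article which ratio the lists use. If the trial ends near 192:128, the allocation reported in the results will not match the published plan, and nothing in the article explains the gap.

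**Working it through.** **Inputs from the article.** Planned arms 200 and 120, total 320; block sizes 5 and 10; strata 3 conditions × 2 sites = 6; site totals 200 and 120; base sample size 180 at 80% power and the 0.05 level; attrition 25%; 12 clinicians targeted. Not given: the within-block ratio, effect size, standard deviation, intraclass correlation (ICC) and the value of the clustering inflation factor.

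**1. The planned ratio.** 200/120 = 5/3, so the bCBT share is 200/320 = 0.625.

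**2. Can a block hold it?** A block of size b needs 0.625 × b bCBT patients.
- b = 5: 3.125, not a whole number.
- b = 10: 6.25, not a whole number.
- b = 8: 5, so 5:3 fits. b = 16: 10, so 10:6 fits.

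In general 5b/8 must be whole, so b must be a multiple of 8.

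**3. What blocks of 5 and 10 can hold.** The ratios open to both sizes, scaled to 320, are:

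| Ratio | bCBT : usual care |
|---|---|
| 1:4 | 64 : 256 |
| 2:3 | 128 : 192 |
| 3:2 | 192 : 128 |
| 4:1 | 256 : 64 |

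A block of 10 alone also allows 7:3, which is 224:96. The nearest to plan is 3:2. It differs by 8 patients in each arm: 8/200 = 4.0% of bCBT and 8/120 = 6.7% of usual care.

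**4. Could incomplete last blocks explain the gap?** This was simulated with six strata, blocks of 5 and 10 at 3:2, the stated site totals and 40,000 trials for each of two assumed condition mixes (equal thirds, and 50/30/20). Under both mixes the bCBT arm averaged 192 with a standard deviation of 1.5, a 95% range of 189 to 195 and a maximum of 198. No simulated trial reached 200.

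**5. Are 200 and 120 just rounded figures?** They fit the sample-size text well. Half of 180 is 90, and 90/0.75 = 120 for usual care. Then 120 × 5/3 = 200 for bCBT, which corresponds to a clustering inflation of 1.67 in that arm only. This route is inferred, since the article does not show it, but it suggests that 5:3 was deliberate.

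**6. Effect on power (assumption-based).** Take the inflation of 1.67 as a design effect and solve 1.67 = 1 + (m − 1) × ICC.
- m = 200/12 = 16.7 patients per clinician gives ICC = 0.043.
- m = 150/12 = 12.5 (after attrition) gives ICC = 0.058.

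Calibrate the effect so that power is 80% at 200:120, using a two-sided normal approximation. After 25% attrition the arms are 150 and 90 as planned, or 144 and 96 at 3:2.
- *Fixed design effect.* The variance factor is 1.667/n1 + 1/n2. It is 0.02222 at (150, 90) and 0.02199 at (144, 96). Power goes from 80.0% to 80.4%.
- *Twelve clinicians, ICC 0.058.* The variance factor is (1 − ICC)/n1 + ICC/12 + 1/n2. It is 0.02222 at (150, 90) and 0.02179 at (144, 96). Power goes from 80.0% to about 80.8%.

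Both routes show power essentially unchanged, very slightly higher at 3:2.

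**The case against.** The strongest objection is that the article never states a within-block ratio, so the conflict depends on assuming one ratio for every block. A mixed scheme could average 5:3. For example, with a quarter of patients in 7:3 blocks of 10 and the rest at 3:2, the bCBT share is 0.25 × 0.70 + 0.75 × 0.60 = 0.625. That is arithmetically correct, and it is why the point is limited to a constant ratio. But such a scheme would be unusual and the article describes none. The article condenses a fuller protocol, so leaving out the within-block ratio is not itself an error. The finding is that the numbers it does print disagree.

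A second objection is that little follows from this. That stands. Analysis is by randomized group, the total of 320 is unchanged, and power barely moves.

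A reader might go further and infer that staff will have to override the list to reach the targets. At 3:2, usual care reaches 120 at about patient 300 (180:120), so ending at 200:120 would mean giving bCBT to all of the last 20. The article does not support that inference. It nowhere says that an arm closes at 200 or 120, it presents 320 as a recruitment target, and it describes concealed envelopes opened only once eligibility is settled. The natural course is to follow the list to 320 with random allocation intact.

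**Conclusion.** The mismatch is real. With one ratio for all blocks, 200:120 needs multiples of 8, while blocks of 5 and 10 come closest at 3:2, or about 192:128. Incomplete blocks do not close the gap, and nothing in the article reconciles the figures.

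Its size is a shift of 8 patients between arms. There is no bias if the list is followed, and the power change is under one percentage point. That power figure rests on an inferred ICC of about 0.04–0.06 with 12 clinicians, on inferred evaluable numbers (150 and 90), and on a normal approximation. None of these is stated in the article. The mismatch itself needs none of them.

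This is a minor to moderate specification error. It does not threaten the validity of the comparison.

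**What to change.** Check the SAS lists already generated and state the within-block ratio.

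- If they run 3:2, keep the blocks of 5 and 10. Restate the allocation as 3:2, with expected arms of about 192 and 128, in the abstract, the Methods section and the sample-size text.
- If they used blocks that are multiples of 8, keep 200:120 and correct the stated block sizes.

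In either case, follow the existing list to 320 without capping or overriding an arm.

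Do not change the ratio for the remaining patients. That would tie treatment arm to calendar time and could still miss the target. For illustration, if half the trial had been allocated at 3:2 (96:64) and the other 160 patients at 5:3 (100:60), the arms would end at 196:124.

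The cost is a look at the lists and a wording correction. No extra patients are needed, and under the assumptions above no power is lost.
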